**Methods/design:**

Twenty-five CRTs from eight NHS Trusts across England will be recruited to this cluster-randomised trial: 15 CRTs will be randomised to receive the service improvement programme over a 1-year period, and ten CRTs will not receive the programme. Data will be collected from 15 service users and all clinical staff from each participating CRT at baseline and at the end of the intervention. Service use data will be collected from the services’ electronic records systems for two 6-month periods: the period preceding and the period during months 7-12 of the intervention. The study’s primary outcome is service user satisfaction with CRT care, measured using a client satisfaction questionnaire. Secondary outcomes include the following: perceived continuity of care, hospital admission rates and bed use, rates of readmission to acute care following CRT support, staff morale, job satisfaction, and general health. The adherence of the services to a model of best practice will be assessed at baseline and follow-up. Outcomes will be compared between the intervention and control teams, adjusting for baseline differences and participant characteristics using linear random effects modelling. Qualitative investigations with participating CRT managers and staff and programme facilitators will explore the experiences of the service improvement programme.

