## Analysis

### 1) Service user experience

We will test the hypothesis that participant satisfaction with the crisis resolution team, measured by the client satisfaction questionnaire [38] is greater in the teams that have implemented the Service Improvement Programme than control teams. This will be analysed using a multivariate linear random effects model with a random effect for CRT (mixed model), controlling for the mean baseline client satisfaction questionnaire score by CRT. Experiences of continuity of care, measured using Continu-um [43], will also be compared between those receiving and those not receiving the intervention.

Second, we will explore, using random effects modelling with a random effect for CRT, the extent to which the team fidelity score can explain variations in individual satisfaction with care.

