### 2) Service use

We will use routine data to compare service use patterns between teams that have received the Service Improvement Programme and the control teams. Data on admission rate, bed use, and population size will be measured over 6-month periods before and after intervention introduction. We will also explore whether there is any evidence of differences between intervention and control areas in extent of change in rates of compulsory detention under the Mental Health Act and of readmissions within 6 months of an initial admission to acute care. Other routinely collected indicators of CRT functioning, such as referral sources and caseload composition will also be examined. Data will be analysed using Poisson random effects modelling. Either bed use or admission rate will be set as the exposure variable as appropriate.

If differences between the two groups are found, national reference costs will be applied to resource use (admission, bed days and re admissions) to calculate the cost difference between resource kit implementation and control areas. A difference in difference model will be used, looking at before and after effects in the two areas using the most appropriate statistical model as determined by Akaike information criteria (AIC) and Bayesian information criteria (BIC) values. This is likely to be a general linear model with log link and family gamma. The model will take the same form as the Poisson model above.

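### The cost comparison is fixed as difference-in-differences although the teams are randomised; adjusting follow-up cost for the team's baseline value would be more efficient and would not over-correct chance imbalance.

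*Protocol article*

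**What the plan says.** All of this is in the Protocol article.

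- **Costs** (Analysis, 2) Service use). If the arms differ in service use, reference costs are applied and "A difference in difference model will be used, looking at before and after effects in the two areas". AIC and BIC choose the statistical model: "This is likely to be a general linear model with log link and family gamma". The section then adds "The model will take the same form as the Poisson model above".
- **Service use** (same section). "Data on admission rate, bed use, and population size will be measured over 6-month periods before and after intervention introduction". For the model: "Data will be analysed using Poisson random effects modelling". No baseline covariate is named. An exploratory aim is to look for "differences between intervention and control areas in extent of change in rates of compulsory detention" and in rates of readmission.
- **Primary outcome** (Analysis, 1) Service user experience). Follow-up satisfaction is modelled "controlling for the mean baseline client satisfaction questionnaire score by CRT".
- **Abstract, Methods/design.** "Outcomes will be compared between the intervention and control teams, adjusting for baseline differences and participant characteristics", a statement tied there to linear random effects models.
- **Design** (Randomisation; Sample, 2) Service use; Measures, 2. Service use). Teams are randomised 15 to 10, stratified by Trust. Cohort 1 is one month of CRT admissions per team, followed for six months. Cohort 2 is all acute inpatient admissions from the catchment over six months. Both are taken at baseline and at follow-up.

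**The concern.** Difference-in-differences is designed for areas that were not randomised, where a lasting difference between groups has to be subtracted out. In this trial any baseline difference between arms is due to chance. The efficient use of the baseline is as a covariate with an estimated coefficient, which is how the protocol treats its primary outcome. The article gives no reason to treat costs differently.

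Fixing the coefficient at 1 has two consequences. The noise in the baseline period enters the effect estimate at full weight, which costs precision when there are only 25 teams. And if one arm happens to start high, its expected fall back towards the mean is counted as part of the effect, with the reverse if it starts low. At stake is the precision of the cost estimate, and how far it depends on the luck of the baseline.

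**Working it through.** **Inputs from the document:** 15 and 10 randomised teams; a baseline and a follow-up period for each; ICC 0.05 (Sample size, stated for satisfaction only).

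**Assumed, because the document gives no figure:** rho, the before-after correlation of team values; two-sided alpha 0.05; equal team variance in both periods; for Cohort 1, 20-50 users per team-month and a cluster autocorrelation (CAC) of 0.8-1. Trust stratification is ignored.

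**1. The plan's own figure.** No power is stated for service use or costs. The only figure to reproduce is the primary one, and this point does not depend on it. The design effect is 1 + 14 × 0.05 = 1.70. Power for 3.5 points with SD 7.0 and 225 v 150 users is then 95.3% (normal approximation, two-sided), against 97% stated. The difference detectable with 80% power is 0.385 SD, against just over one-third stated. The agreement is close enough.

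**2. Variance.** In units of σ²(1/15 + 1/10), with σ² the between-team variance:
- difference-in-differences: 2(1 − rho)
- baseline-adjusted: 1 − rho²
- follow-up only: 1

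The ratio of the first to the second is 2(1 − rho)/[(1 − rho)(1 + rho)] = 2/(1 + rho). Below rho = 0.5, 2(1 − rho) exceeds 1, so difference-in-differences is then less precise than ignoring the baseline.

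**3. Power.** Noncentral t, 15 v 10 teams, with the effect set so that difference-in-differences has 80% power (23 df). The baseline-adjusted variance is inflated by 1 + 1/21 for the estimated slope and tested on 22 df.

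| rho | Variance ratio 2/(1+rho) | Ratio after slope penalty | Baseline-adjusted power |
|---|---|---|---|
| 0.3 | 1.54 | 1.47 | 92% |
| 0.4 | 1.43 | 1.36 | 90% |
| 0.5 | 1.33 | 1.27 | 88% |
| 0.6 | 1.25 | 1.19 | 86% |
| 0.7 | 1.18 | 1.12 | 84% |
| 0.8 | 1.11 | 1.06 | 82% |
| 0.9 | 1.05 | 1.005 | 80% |

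At rho = 0.95 the penalised ratio is 0.98, so the extra slope then costs slightly more than it returns.

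**4. Simulation.** 4,000 trials per scenario; Poisson counts with mean 100, team log-rate SD 0.3 and true rate ratio 0.8 (all assumed); team log rates analysed. Here rho is the correlation of the underlying team log rates. Power for difference-in-differences v baseline-adjusted was 29% v 40% (rho 0.3), 33% v 42% (0.5), 47% v 55% (0.7) and 75% v 77% (0.9). Both estimators were centred on the true effect, with type I error of about 5%.

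**5. Chance imbalance.** The SD of the chance baseline difference between arms is √(1/15 + 1/10) = 0.41 team SDs. Given such a difference, the difference-in-differences estimate moves by about −(1 − rho) times it. For a one-SD imbalance at rho 0.5 this is 0.5 × 0.41 = 0.20 team SDs. Simulated slopes with no true effect were −0.74, −0.55, −0.39 and −0.18 at rho 0.3, 0.5, 0.7 and 0.9; the baseline-adjusted slopes were about 0.

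**6. Which rho is plausible.** For Cohort 1 team means, rho = CAC × m × 0.05/(1 + (m − 1) × 0.05), with m users per team-month:
- m = 20, CAC 0.8: 0.8 × 1/1.95 = 0.41
- m = 50, CAC 1: 2.5/3.45 = 0.72

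By step 3, that range is a gain of about 4-10 points. For whole-catchment rates over six months (Cohort 2), rho may be 0.8 or more; at 0.8-0.9 the gain is 0-2 points.

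**The case against.** The strongest reply is that little is lost where the choice is explicit. Costs are built from admissions, bed days and readmissions. The admission and bed-use data match the whole-catchment Cohort 2, where rho may be high and the gain is 0-2 points. The larger gain applies to Cohort 1, under an ICC borrowed from satisfaction and assumed caseloads. Costing is also secondary, takes place only if the arms differ, and has no power target. All of this stands and limits the weight of the point. It does not supply a reason to prefer difference-in-differences under randomisation.

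The AIC/BIC step is a weaker defence. It leaves the distribution and link open, but the before-after contrast is already fixed.

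Two stronger readings are tempting, and the document does not support them:

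- **That the Poisson service-use models are also difference-in-differences.** A reader might infer this from "The model will take the same form as the Poisson model above" and from the wording about extent of change. But the Poisson paragraph never names that method. Same form may mean only the random effect and covariates. Extent of change describes an exploratory question, and in a linear model, adjusting change for baseline gives the same arm effect as adjusting follow-up for baseline. The abstract speaks of baseline adjustment, although for linear models.
- **That the cost result will be biased or its error rate wrong.** Over randomisations both estimators are unbiased with correct type I error. The over-correction is conditional on a chance imbalance and can go in either direction.

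**Conclusion.** The point holds for the cost comparison. The article fixes a valid but less efficient estimator in a randomised trial that already plans to collect the baseline it needs. The large-sample variance penalty is 2/(1 + rho). The practical gain from changing is about 0-2 points of power if team values are stable (rho 0.8-0.9) and about 4-10 points if they are noisy (rho 0.4-0.7), as may hold for Cohort 1. Adjustment also removes the dependence on chance baseline imbalance, which is about (1 − rho) times its size. The size rests on an undocumented rho. The finding concerns efficiency and conditional bias in a conditional secondary analysis; the primary analysis already adjusts for baseline.

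For the Poisson models the finding is only that the text leaves their use of baseline unclear while making them the template for the cost model.

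**What to change.** In Analysis, 2) Service use:

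1. Make the main cost model one of follow-up cost with arm, the team's baseline-period value (log mean cost under a log link) and the CRT random effect. Alternatively, fit a joint before-after model with the arms' baseline means constrained equal, which randomisation justifies.
2. Keep difference-in-differences as a sensitivity analysis if wanted.
3. State that the Poisson service-use models likewise adjust follow-up for the team's baseline log rate. This fits the primary analysis and the abstract, and it gives the reference to the same form a clear meaning.

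The cost is a change of wording and one model degree of freedom among 25 teams. No data are needed beyond those planned. There is little or no gain where rho is near 0.9 or above.

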### 3) Staff well-being

We will test the hypotheses that the mean staff psychological well-being scores, measured by the General Health Questionnaire [45], and the mean staff burnout scores, measured by the Maslach Burnout Inventory [44], will be lower in CRTs receiving the Service Improvement Programme and that the mean staff job involvement scores, measured by the Work Engagement Scale [47], will be higher in CRTs receiving the Service Improvement Programme. We will use data collected from CRT staff at study baseline before the introduction of the programme to assess whether there are baseline differences between the two groups of teams for which adjustments should be made.

In secondary analyses, we will explore whether staff psychological flexibility scores at baseline, measured using the Work-Related Acceptance and Action Questionnaire [46], predicts staff morale and job satisfaction following implementation of the Service Improvement Programme and whether psychological flexibility scores change following implementation.

### 4) Qualitative and process evaluation

#### Process data

Fidelity reviews: We will provide descriptive data regarding changes in the team fidelity scores over the 1-year study period. We will explore the extent to which team fidelity score can explain variations in individual satisfaction with care. This analysis will use linear random effects modelling, with a random effect for CRT.Descriptive data on the number of implementation activities at each site and the proportion of total implementation activities of each type will be reported for each CRT team.We will also report whether the following implementation structures recommended as part of the Service Improvement Programme were achieved at each intervention CRT: scoping day; development of a service improvement plan; formation of a service improvement group; whether the SIG met at least six times during the study; attendance of team/Trust representatives at a learning collaborative day.For all 25 teams, we will report whether any other major service improvement initiatives took place during the study intervention year.The online resource kit used by the CRT staff will be monitored via Google Analytics, which captures time spent on individual pages and document downloads.

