The US National Implementing Evidence-Based Practices Project (EBP) [28, 29] offers a model for evaluating and promoting quality improvement in complex service-level mental health interventions. Integral elements of the EBP approach are service reviews using a fidelity measure that assesses how far services are achieving a model of good practice and utilisation of a resource kit to support implementation and quality improvement [30]. Resource kits typically consist of guidance, training materials, and coaching and support for service managers and staff, designed to help services address areas where high model fidelity has not been achieved. Modelling of factors associated with successful implementation of evidence-based practices has helped to theoretically underpin the EBP implementation model [31, 32]. Attention to workforce development and training may in itself be insufficient to achieve high fidelity implementation of complex mental health interventions: securing leadership support, organising workflow (service structures and organisation) to support implementation, and providing feedback to reinforce implementation successes are also required [31]. Access to technical assistance that enables understanding of the specific requirements of a complex intervention can also facilitate implementation [32]. The EBP programme has successfully developed fidelity scales and implementation resources for a range of service-level interventions including supported employment [33] and assertive community treatment [34]. Previous studies have found correlations between fidelity to an evidence-based practice and better client outcomes [35, 36]. CRTs are comparable with models in the EBP project because trial evidence exists for their efficacy in the right conditions. A CRT fidelity scale was developed in an earlier part of this programme of research (The CORE Study) [37]. This trial will test the effectiveness of the CORE CRT Service Improvement Programme in helping CRTs improve outcomes and achieve high model fidelity.

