## Aims

This trial tests the CORE CRT Service Improvement Programme in a cluster-randomised trial. CRTs randomised to the intervention arm will receive the Service Improvement Programme over a 1-year period, and control CRTs will not receive the intervention. The study aims to investigate whether a CRT Service Improvement Programme can improve service users’ experience of CRT care, reduce acute service use, and improve CRT staff well-being. The primary outcome is service user satisfaction, measured using The Client Satisfaction Questionnaire (CSQ-8) [38]. We will also explore whether the fidelity scores of the CRT teams receiving the Service Improvement Programme rise over the 1-year intervention period and the associations between team fidelity score and service outcomes. Through a qualitative and process evaluation, we will seek to understand stakeholder experience of the CRT Service Improvement Programme, contextual factors constituting barriers and facilitators to its implementation, and any mechanisms by which it may improve team effectiveness.

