### 4. Qualitative and process evaluation

#### Fidelity reviews

CRT model fidelity will be assessed in all teams at baseline and 1-year follow-up using the CORE CRT Fidelity Scale [37], a 39-item measure yielding a total score ranging from 39–95.

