## Research implications

The main trial results will provide preliminary evidence regarding whether the CORE CRT Service Improvement Programme is effective in increasing model fidelity and improving outcomes in CRTs. The study will also provide the following:Evidence regarding the validity of the CORE CRT fidelity scale. We will explore, through multilevel modelling, whether team fidelity scores relate to important service user and staff outcomes.Evidence regarding the feasibility of implementing the intervention from process data and barriers and facilitators to implementation from the qualitative evaluation, which can help understand any mechanisms of change and inform future implementation programmes.

Implementation represents the biggest challenge to translating research knowledge into patient benefit [52]. CRTs exemplify this challenge: trial evidence suggests they can be effective in reducing admissions and enhancing service user experience, but observational studies and audits indicate the benefits of CRT implementation on a national scale may be smaller and less consistent than originally expected [19, 20]. Means of supporting the effective implementation of the CRT model are therefore of high interest to service planners. Through testing a theoretically underpinned, clearly defined, extensive package of implementation resources for CRTs, our trial can provide evidence to address this important issue.

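### The article promises evidence on whether the programme raises team fidelity but plans only descriptive change; a baseline-adjusted comparison between arms needs no new data

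*Protocol article*

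**What the plan says.** The Process data part of the Analysis section states: "We will provide descriptive data regarding changes in the team fidelity scores over the 1-year study period". Its only model that uses fidelity treats the score as an explanatory variable for satisfaction: "We will explore the extent to which team fidelity score can explain variations in individual satisfaction with care". No comparison of fidelity between arms is named there.

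The Aims word the question without a comparator: "We will also explore whether the fidelity scores of the CRT teams receiving the Service Improvement Programme rise over the 1-year intervention period".

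Three other places describe an effect of the programme on fidelity. The background paragraph of the Abstract lists team model fidelity among the things on which the programme's impact will be evaluated. The Background says: "This trial will test the effectiveness of the CORE CRT Service Improvement Programme in helping CRTs improve outcomes and achieve high model fidelity". The Research implications say: "The main trial results will provide preliminary evidence regarding whether the CORE CRT Service Improvement Programme is effective in increasing model fidelity".

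The scores that a controlled comparison needs are collected in both arms. Under Measures: "CRT model fidelity will be assessed in all teams at baseline and 1-year follow-up using the CORE CRT Fidelity Scale". The intervention section confirms that control teams have a review and written report at both times.

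**The concern.** Evidence that a programme increases fidelity is a statement about cause. It needs a comparison with what would have happened without the programme. The change over one year in the programme teams is not that comparison, for three reasons found in the article itself:

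- Scores may drift in all teams over the year.
- Other major service improvement initiatives are expected, and the article plans to record them in all 25 teams.
- The baseline review and written report may themselves prompt improvement, and control teams receive both.

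Fidelity is the mechanism through which the programme is meant to work, and the Discussion says that measured fidelity change will help to explain the trial's outcomes. If the fidelity result is read from programme teams alone, a rise that both arms share could be credited to the programme. The interpretation of the satisfaction result would then rest on a wrong account of the mechanism.

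**Working it through.** The article gives no target, standard deviation (SD) or power for fidelity, so there is no stated figure to reproduce. Its sample-size statement concerns satisfaction and does not bear on this point.

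**Plan against claim.** The analysis sections for service user experience, service use and staff well-being each set programme teams against control teams. The fidelity-change sentence does not, although the Abstract, Background and Research implications attach an effect conclusion to fidelity. The mismatch lies within the article.

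**What a controlled comparison would deliver.** Inputs from the article: 15 programme and 10 control teams; eight Trusts, by which randomisation is stratified (Abstract, Randomisation). Assumptions: two-sided 5% level; correlation r between baseline and 12-month team scores of 0 to 0.7, because none is given.

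- Standard error of the adjusted difference, in SDs of the team score: SE = √[(1 − r²)(1/15 + 1/10)]. For r = 0.5: √(0.75 × 0.1667) = 0.354.
- Degrees of freedom with Trust as indicator terms: 25 − 1 (intercept) − 1 (arm) − 1 (baseline) − 7 (Trust) = 15. Without Trust: 22.
- Half-width of the 95% interval: 2.131 × SE at 15 degrees of freedom. For r = 0.5: 0.75.
- Difference detectable with 80% power, from the noncentral t distribution; closely, (2.131 + 0.866) × SE. For r = 0.5: 2.997 × 0.354 = 1.06.

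| r | SE | 95% half-width (15 df) | Detectable at 80% (15 df) | Detectable at 80% (22 df) | Power for 1 SD (15 df) |
|---|---|---|---|---|---|
| 0 | 0.408 | 0.87 | 1.22 | 1.20 | 63% |
| 0.3 | 0.389 | 0.83 | 1.17 | 1.14 | 67% |
| 0.5 | 0.354 | 0.75 | 1.06 | 1.04 | 75% |
| 0.7 | 0.292 | 0.62 | 0.87 | 0.85 | 89% |

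The formula charges the Trust terms only in degrees of freedom. It ignores uneven allocation within Trusts, which would widen the interval, and variance explained by Trust, which would narrow it.

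**How easily a common shift looks like a programme effect.** The article plans no significance test of the before-after change, so this is only an illustration. Suppose both arms shift by s SDs and the programme does nothing. A paired t-test in 15 teams then has noncentrality s√15 / √[2(1 − r)] on 14 degrees of freedom. The chance of a significant rise, nominally 2.5% in that direction, is:

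| Assumed shift s | r = 0.3 | r = 0.5 | r = 0.7 |
|---|---|---|---|
| 0.25 SD | 12% | 15% | 21% |
| 0.50 SD | 33% | 44% | 64% |
| 0.75 SD | 63% | 77% | 94% |

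The comparison between arms removes such a shift, because it is present in both.

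**The case against.** The strongest reply is that the article is modest about fidelity. The aim is to explore, the evidence is called preliminary, the analysis sits under process evaluation, and fidelity is not among the secondary outcomes that the Abstract lists. With 25 teams and no blinding, descriptive reporting is defensible. This lowers the weight of the point. It does not reconcile the descriptive plan with the effect statements, and those in the Abstract and Background carry no such qualifier.

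A second reply is that the Abstract follows its fidelity sentence with a general statement that outcomes will be compared between arms with adjustment for baseline. That could be read to cover fidelity, but it does not name it, and the analysis section does not carry it through.

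Three stronger readings are tempting and are not supported:

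- A reader might infer that only programme teams will be described, so that a null satisfaction result could never be traced to unchanged or changed fidelity. The Process data sentence is not restricted to one arm. Descriptive changes shown for both arms would give some of that information, though no adjusted estimate or interval is planned.
- A reader might infer that excluding teams with a mean item score of 4 or higher makes scores regress between baseline and 12 months. The exclusion used an earlier survey, and the trial's baseline reviews are described separately. Regression would then fall largely between survey and baseline, and nothing says that the survey score serves as baseline.
- A reader might infer that the model of satisfaction on fidelity leaves out arm. The article gives only the model class and the random effect. Its covariates are unstated, and that is commonly left to the analysis plan.

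**Conclusion.** The point holds as a mismatch between planned analysis and intended conclusion. A descriptive change, with an aim worded for programme teams only, cannot by itself show that the programme increases fidelity. The comparison that could address this uses scores already due to be collected.

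Its weight is moderate: the aim is exploratory, and the primary and listed secondary analyses are untouched. The controlled comparison would also be imprecise, with a 95% half-width of 0.62 to 0.87 SD and a detectable difference of 0.87 to 1.22 SD for an assumed correlation of 0.7 down to 0. The article gives no target change in fidelity, so whether a difference of that size is plausible cannot be judged from it.

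The comparison would not remove bias from reviewers who know the allocation, since the article makes no arrangements for blinding. Nor would it remove dilution from contamination within Trusts, which the Limitations acknowledge.

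**What to change.** Add one sentence to the Process data analysis: as an exploratory analysis, the 12-month total fidelity score will be compared between arms by team-level linear regression on arm and baseline fidelity score, accounting for the Trust stratification, and reported as an adjusted difference with a 95% confidence interval. State beside it that reviewers are not blinded. Reword the Aims sentence so that it names the control teams as comparator.

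If the sponsor prefers to keep the analysis descriptive, limit the Abstract, Background and Research implications to describing change in fidelity, and present that change for both arms.

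Either route is a change of wording. The first adds one regression on 25 rows and no data collection. It is best fixed before the 12-month scores are examined.
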